##### 12.2.1.3 Quantity of study drug administered

Total drug administered, number of administrations, number and length of interruptions, and number of discontinuations will be calculated for each patient and summarised.

#### 12.2.2 Analysis of Secondary Outcome Measures

Repeated measures numerical outcomes will be analysed by hierarchical models, with patient-level effects to account from baseline value and progression with respect to time. Transformations of the time variable and smoothed terms (e.g. splines) will be considered if the outcomes are found to be non-linear in time

ALSFRS-R and ALSAQ-40 are very granular ordinal variables. They have 49 and 101 levels respectively so a categorical analysis is not feasible. There are many instances in the literature of these outcomes being analysed as numbers. As such, we will analyse these outcomes as numbers.

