### 1.2.3 Choice of treatment

Patients will receive 2mg/kg of ILB subcutaneously for ten weeks once per week in the first instance, during out-patient appointments at site.

Data from toxicity studies performed in mice, rats and monkeys, data from studies in healthy subjects and diabetes patients, and additional information obtained from the literature with similar substances, indicate that the proposed doses have a favourable safety profile.

In the two-part dose-finding study in healthy volunteers clinical study LMW-DS-102 using LMW-DS, dose proportionality of ILB was indicated by an apparent linear increase in  $C_{max}$  with increasing doses (3-24 mg/kg), and also  $AUC_{inf}$  appeared to increase linearly with increasing dose (see Table 1). Further,

the pharmacokinetic parameters in study LMW-DS-102 correlated well with the results from other healthy volunteer studies, LMW-DS-101 (4.5 mg/kg) and TM-104 (6 mg/kg, i.v. and s.c.). Based on these results, it was considered reasonable to expect that the pharmacokinetics of ILB is approximately linear also at 2 mg/kg, and thus it could be anticipated that a dose of 2 mg/kg would after s.c. administration give a  $C_{max}$  around 5 mg/L and the AUC would be around 30 h\*mg/L.

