**Table 1 Mean pharmacokinetic exposure parameters in plasma from healthy volunteers**

| Dose #
(mg/kg)                | C max
(mg/L) | AUC inf (h*mg/L) | Treatment                                                            | Clinical Study No. |
|----------------------------------|----------------------------|-----------------------------|----------------------------------------------------------------------|--------------------|
| 4.5                              | 32.1                       | 65.5                        | 1.5 mg/kg, i.v.
bolus and 3 mg/kg,
20 minutes i.v.
infusion | LMW-DS-101         |
| 6                                | 63.1                       | 106                         | 10 min i.v. infusion                                                 | TM-104             |
| 6                                | 14.6                       | 92                          | s.c.                                                                 |                    |
| 3                                | 29.4                       | NC                          | 10 minutes i.v.
infusion                                          | LMW-DS-102         |
| 6                                | 70.0                       | 154*                        |                                                                      |                    |
| 9                                | 76.8                       | 156*                        |                                                                      |                    |
| 12                               | 120                        | 264                         |                                                                      |                    |
| 15                               | 171                        | 337                         |                                                                      |                    |
| 18                               | 159                        | 330                         |                                                                      |                    |
| 24                               | 209                        | 457                         |                                                                      |                    |

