### 2.4 Secondary Outcome Measures

Our secondary outcome measures will provide data on patient function and disease progression

- Revised ALS Functional Rating Scale (ALSFRS-R)
  - o This is a functional rating scale, including assessments of communication, mobility, feeding, dressing and respiration.
- ALS Assessment Questionnaire (ALS AQ-40)
  - o This patient-reported outcome measures the subjective well-being of patients. It is broader than ALSFRS-R and adds assessment of emotional reactions.
- Urinary p75ECD
  - o This is a biological fluid-based biomarker of ALS disease progression
- PK ILB in plasma following administration
  - o This quantifies the amount of drug detectable in the blood after administration over time
- NfL in plasma
  - o This is a blood-based biomarker for neurodegeneration

---

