## 7.4 Sample Collection

### 7.4.1 Blood samples

#### 7.4.1.1 Pharmacokinetic samples

For all patients, blood samples for the determination of ILB levels will be collected as detailed in the Schedule of Assessments in the study protocol.

Samples (plasma) for PKs should be collected from whole blood, collected in anti-coagulant-treated Vacutainer tubes (3.2% sodium citrate (blue-topped)). Serum should not be prepared.

Samples for ILB measurements should be sent (single/few batches) to:

Eurofins BioPharma Product Testing Munich GmbH  
[name]  
[name]  
[name]  
Germany  
[contact] (phone)  
[[contact]](mailto:[contact])

| Time Point                                   | Blood Sample Type | Volume of blood (ml) |
|----------------------------------------------|-------------------|----------------------|
| Pre-dose (30 minutes prior to ILB injection) | Blood Plasma      | 14                   |
| 30 minutes post-injection                    | Blood Plasma      | 3.5                  |
| 60 minutes post-injection                    | Blood Plasma      | 3.5                  |
| 120 minutes post –injection                  | Blood Plasma      | 3.5                  |
| 150 minutes post-injection                   | Blood Plasma      | 3.5                  |
| 180 minutes post-injection                   | Blood Plasma      | 3.5                  |
| 240 minutes post-injection                   | Blood Plasma      | 3.5                  |
| 360 minutes post-injection                   | Blood Plasma      | 3.5                  |

Please use the current version of the laboratory manual for further information.

The remaining PK samples should be stored in a -80°C freezer and will be shipped in batches for HGF measurement (exploratory biomarker) to the Neuregenix laboratory.

**7.4.1.2 NfL levels** (performed prior to administration of study drug)

- 10mls Whole Blood collected in EDTA-treated Vacutainer tubes (lavender/purple top) (to allow for 4-5mls plasma for analysis).

Samples should be stored in a -80°C freezer and will be shipped in batches to Sahlgrenska University Hospital, (Neurokemi lab), Gothenburg, Sweden

Please see the latest version of the laboratory manual for further information

**7.4.1.3 Exploratory Biomarker Blood Samples** (performed prior to administration of study drug)

Exploratory biomarker samples for:

- HPLC analysis of purines, pyrimidines, oxidative/nitrosative stress compounds (n = 60)

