### 12.2 Analysis of Outcome Measures

Numerical outcomes will be summarised and presented as means and standard deviations where the outcome is approximately normal; or median and inter-quartile ranges where non-normal.

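### Section 12.2.2's blanket rule puts the Week 1 plasma ILB profile under a baseline-and-progression model that does not report Cmax or AUC and misdescribes between-patient exposure

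*Protocol*

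**What the plan says.** Protocol 2.4 lists plasma ILB among the secondary outcomes and describes it thus: "This quantifies the amount of drug detectable in the blood after administration over time". Section 7.4.1.1 sets eight samples, from pre-dose to "360 minutes post-injection", and the main schedule marks PK at Week 1 only.

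Section 12.2.2 has one rule for repeated numerical secondary outcomes: "Repeated measures numerical outcomes will be analysed by hierarchical models, with patient-level effects to account from baseline value and progression with respect to time". It adds: "Transformations of the time variable and smoothed terms (e.g. splines) will be considered if the outcomes are found to be non-linear in time". The only outcomes it then discusses are ALSFRS-R and ALSAQ-40. The general rule in 12.2 reads: "Numerical outcomes will be summarised and presented as means and standard deviations where the outcome is approximately normal", with medians and quartiles otherwise. Nowhere does the protocol name Cmax, tmax or AUC as something to derive in this trial.

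The dose rationale in 1.2.3 is written in those terms. From the data in Table 1, "it was considered reasonable to expect that the pharmacokinetics of ILB is approximately linear also at 2 mg/kg", and 2 mg/kg s.c. is expected to give a Cmax "around 5 mg/L and the AUC would be around 30 h\*mg/L".

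**The concern.** Plasma ILB is numerical, repeated and secondary, so 12.2.2 covers it as written. The rule's two patient-level ingredients do not fit it. Sampling surrounds the first dose in patients not previously given ILB, so the pre-dose level should be zero in everyone and there is no baseline difference to model. The profile then rises and falls within a day, so there is no progression either. The amendment log for version 8.0 records PK being added to 2.4 and lists no change to Section 12. That may explain the mismatch.

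At stake is a useful description of exposure in ALS patients at this dose and route. The expected values come from healthy men given three times the dose. Treatment and recruitment have ended for good (1.2.4), so these profiles are all the trial will have and only their analysis can still be improved.

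**Working it through.** **1. The plan's own figure.** Table 1 gives 14.6 mg/L and 92 h*mg/L for 6 mg/kg s.c. Scaling by 2/6:
- Cmax = 14.6 x 2/6 = 4.87 mg/L (stated: about 5)
- AUC to infinity = 92 x 2/6 = 30.7 h*mg/L (stated: about 30)

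Both reproduce.

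**2. An illustrative profile (assumption).** I take a one-compartment curve with first-order absorption, C(t) = AUC x ke x ka/(ka - ke) x [exp(-ke t) - exp(-ka t)], matched to both values. Section 1.1.5 gives a half-life of about 3 h after infusion and says it is longer after s.c. dosing, without a figure. I therefore use 2 to 4.3 h. The upper end is close to the most this curve form allows: its peak cannot exceed ke x AUC, so ke is at least 4.87/30.7 = 0.159 per hour and the half-life at most 0.693/0.159 = 4.4 h.

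At 3 h, ka = 1.29 per hour, and the concentrations in mg/L are:

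| Hours | 0 | 0.5 | 1 | 2 | 2.5 | 3 | 4 | 6 |
|---|---|---|---|---|---|---|---|---|
| mg/L | 0 | 3.16 | 4.47 | 4.78 | 4.50 | 4.14 | 3.38 | 2.15 |

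**3. What the planned samples give directly.** At 3 h:
- Observed Cmax = 4.78 mg/L.
- Trapezoidal AUC(0-6 h) = 0.79 + 1.91 + 4.63 + 2.32 + 2.16 + 3.76 + 5.53 = 21.1 h*mg/L.
- Tail: the log-linear slope over the last three points is about 0.218 per hour, so AUC to infinity = 21.1 + 2.15/0.218 = about 31.0 h*mg/L.

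| Half-life (h) | Observed Cmax (mg/L) | AUC(0-6 h) (h*mg/L) | Share of 30.7 | AUC to infinity (h*mg/L) |
|---|---|---|---|---|
| 2.0 | 4.84 | 22.1 | 72% | 34.2 |
| 3.0 | 4.78 | 21.1 | 69% | 31.0 |
| 4.0 | 4.87 | 18.9 | 62% | 30.0 |
| 4.3 | 4.57 | 17.9 | 58% | 29.6 |

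Cmax can be checked against 4.87. Between 28% and 42% of the area to infinity lies beyond the last sample.

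**4. The 12.2.2 model with time linear.** A straight line through the 3 h profile is 3.10 + 0.094t. Its highest fitted value is 3.7 mg/L, so it misses the peak.

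**5. The 12.2.2 model with splines.** I simulated 15 patients per data set around the 3 h curve, assuming variability of 30% in level, 30% in absorption, 15% in elimination and 10% residual. The model had a cubic spline in time with five degrees of freedom.
- Mean curve, random intercept, 20 data sets: peak 4.9 mg/L and AUC(0-6 h) 21.8, against 5.1 and 21.5 from averaging the patients' own values. The mean is recovered.
- Patient level, random intercept and slope, 100 data sets: fitted pre-dose values averaged from -1.4 (lowest patient) to 2.2 mg/L (highest), where the truth is zero.
- The between-patient SD of Cmax averaged 1.0 mg/L from the fitted curves and 1.7 from observed values. The true SD under these assumptions is 1.6.

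Many of the fits with a random slope gave convergence warnings. A random intercept alone gave nearly the same figures (-1.4 to 2.1 mg/L; SD 1.0), so the result does not hang on the slope.

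**The case against.** The strongest reply has four parts.

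- **Splines are allowed.** A profile that rises and falls is the non-linear case for which 12.2.2 offers them, and the fitted curve has a maximum and an area. This stands for the mean curve. It does not reach the patient level: splines are only to be considered, and the effects named for each patient are baseline and progression. Patient-specific smooth terms or a compartmental mixed model would do better, but the text does not describe either.
- **PK parameters belong in the SAP or a PK plan.** Silence here would indeed be no finding. But 12.2.2 is not silent: its rule is wide enough to catch PK, and a later plan using non-compartmental analysis would depart from it as written. The surrounding text does suggest that disease measures were in mind, which keeps the point small.
- **Nothing stops anyone deriving Cmax and AUC.** This stands. They are one value per patient, and 12.2 already says how such values are summarised. A reader might infer that the expected exposure cannot be checked in this trial. The documents do not support that.
- **The trial does not set out to test 5 mg/L and 30 h*mg/L.** This also stands. They are expectations in the dose rationale, and no objective commits to testing them. The comparison should be descriptive.

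**Conclusion.** The point holds as a minor one. Section 12.2.2 fixes, for a named secondary outcome, a model whose patient-level terms do not match the data and whose output is not Cmax or AUC. The mean curve is safe if splines are used. What suffers is the description of individual exposure: non-zero fitted baselines, and a Cmax SD about 40% too small in the simulation (1.0 against 1.7). Those sizes rest on the assumed one-compartment shape, 3 h half-life, variability and planned 15 patients, and would differ with the real data.

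It would go too far to say that the planned analysis can yield no exposure figure, or that the check is impossible. The spline curve gives a mean peak and a partial area, and the samples give per-patient values directly. The limit on checking AUC to infinity is the 6 h end of sampling, and rewording 12.2.2 does not remove it.

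**What to change.** In 12.2.2, exempt plasma ILB from the hierarchical model. State that Cmax, tmax and AUC(0-6 h) will be derived for each patient by non-compartmental methods from actual sampling times. Report half-life and AUC to infinity only where the terminal phase supports them, with the extrapolated share shown.

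Summarise across patients, for example by geometric mean, CV and 95% interval. Set Cmax descriptively beside the expected value of about 5 mg/L. Do not set AUC(0-6 h) beside 30 h*mg/L, which is an area to infinity; the protocol gives no expected value for 0-6 h.

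The cost is two or three sentences of analysis wording, with no new samples, visits or change of design.

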### 12.3 Planned Sub Group Analyses

There are no sub-group analyses planned.

### 12.4 Planned Interim Analysis

Interim analyses of safety outcomes and available efficacy outcomes will be presented to the relevant independent oversight committee after the sentinel patients and periodically thereafter.

Proposed analysis for publications will occur at the following end points:

- 
- We propose to conduct and submit for publication an analysis of available primary and secondary outcomes for all fifteen patients after the fifteenth patient has been evaluated to the fullest extent over the initial 10 week dosing period.
- Further analysis of outcomes will be submitted for publication after all patients who continue treatment complete 24 weeks of treatment.

### 12.5 Planned Final Analyses

We will seek to conduct and distribute for publication the final analysis within 6 months of the final protocol assessment of the final patient.

### 12.6 Power Calculations

No sample size calculations have been undertaken. The sample size has been selected based on what is feasible to be recruited at a single centre in a reasonable timeframe for this phase of clinical trial.

## 13. TRIAL ORGANISATIONAL STRUCTURE

### 13.1 Sponsor

The trial is sponsored by the University of Birmingham

### 13.2 Coordinating Centre

The trial is being conducted under the auspices of the Cancer Research UK Clinical Trials Unit (CRCTU), University of Birmingham according to their local procedures.

### 13.3 Trial Management Group

The Trial Management Group (TMG) will be responsible for the day-to-day running and management of the trial and will meet by teleconference or in person as required. Members of the TMG include the Chief Investigator (CI), CRCTU Trial Management Team Leader, Senior Trial Coordinator, Trial Coordinator, Lead Trial Statistician and a Pharmacy representative. The TMG will meet or hold a teleconference every 2nd month during recruitment, or as required.

### 13.4 Trial Steering Committee

This clinical trial will not require a separate stand-alone Trial Steering Committee. Both the Data Monitoring Committee (DMC) and the TMG will undertake traditional roles of the TSC.

### 13.5 Data Monitoring Committee

Data analyses will be supplied in confidence to an independent Data Monitoring Committee (DMC), which will be asked to give advice on whether the accumulated data from the trial, together with the results from other relevant research, justifies the continuing recruitment of further patients. The DMC will operate in accordance with a trial specific charter based upon the template created by the Damocles Group. *The DMC will meet as soon as possible following the recruitment of the first sentinel patient to discuss the data and safety following the recruitment of the first patient. The DMC will meet again as soon as possible following the recruitment of the second sentinel patient. During the general recruitment phase of the trial the DMC is scheduled to meet three monthly via teleconference and annually thereafter.*

Additional meetings may be called if recruitment is much faster than anticipated and the DMC may, at their discretion, request to meet more frequently or continue to meet following completion of recruitment. An emergency meeting may also be convened if a safety issue is identified. The DMC will report directly to the Trial Management Group *TMG* who will convey the findings of the DMC to the funders, *MHRA and sponsor as applicable*. The DMC may consider recommending the discontinuation of the trial if the recruitment rate or data quality are unacceptable or if any issues are identified which may compromise patient safety. The trial would also stop early if any of the Trial Stopping Rules as detailed on page (ix) of the protocol are met.

In the event that the trial is suspended the MHRA and the REC will be advised and recruitment will not recommence until after submission and approval of a Substantial Amendment.

---

## 13.6 Finance

This is a clinician-initiated and clinician-led trial funded by an educational grant from industry (TikoMed). TikoMed will be supplying the investigational medicinal product (IMP), ILB free of charge to all individual NHS Trusts that will be directly treating patients as part of this clinical trial.

### 13.6.1 Payments to individual NHS Trusts (per-patient payment)

Refer to the Clinical Study Site Agreement for details.

## 14. ETHICAL CONSIDERATIONS

The trial will be performed in accordance with the recommendations guiding physicians in biomedical research involving human subjects, adopted by the 18th World Medical Association General Assembly, Helsinki, Finland, June 1964, amended at the 48th World Medical Association General Assembly, Somerset West, Republic of South Africa, October 1996.

The trial will be conducted in accordance with the Research Governance Framework for Health and Social Care, the applicable UK Statutory Instruments, (which include the Medicines for Human Use Clinical Trials 2004 and subsequent amendments and the Data Protection Act 1998 and Good Clinical Practice (GCP). This trial will be carried out under a Clinical Trial Authorisation in accordance with the Medicines for Human Use Clinical Trials regulations. The protocol will be submitted to and approved by the main Research Ethics Committee (REC) prior to circulation.

Before any patients are enrolled into the trial, the Principal Investigator at each site is required to obtain local R&D approval. Sites will not be permitted to enrol patients until written confirmation of R&D approval is received by the Trials Office.

It is the responsibility of the Principal Investigator to ensure that all subsequent amendments gain the necessary local approval. This does not affect the individual clinicians' responsibility to take immediate action if thought necessary to protect the health and interest of individual patients.

## 15. CONFIDENTIALITY AND DATA PROTECTION

Personal data recorded on all documents will be regarded as strictly confidential and will be handled and stored in accordance with the General Data Protection Regulation and Data Protection Act 2018 for health and care research. The University of Birmingham, as the Sponsor for the ALS study, will be using information from patient medical records in order to undertake this trial and will act as the data controller for the study. This means that the University of Birmingham are responsible for looking after the information and using it properly. University of Birmingham and the NHS will keep identifiable information about the patients for at least 25 years after the study has finished, to allow the results of the study to be verified if needed.

All information collected by the Sponsor will be securely stored at the Trials Office at the University of Birmingham on paper and electronically and will only be accessible by authorised personnel. The only people in the University of Birmingham who will have access to information that identifies a patient will be people who manage the study or audit the data collection process.

The NHS will use the patient's name and contact details to contact patients about the research study, and make sure that relevant information about the study is recorded for their care, and to oversee the quality of the trial. With the patient's permission, the research team (at site) will notify the patient's GP that they intend to participate in the study.

With the patient's consent, their *full name (on consent form only), initials and date of birth will be collected at trial entry*. The research team (at site) will send a copy of the signed consent form in the post to the Trials Office. *This will be used to perform in-house monitoring of the consent process.*

In routine communication between the hospital and the Trials Office, the patient will only be identified by study number, initials and date of birth. Data may be provided to the Trials Office on paper or electronically.

By taking part in the study, the patient will be agreeing to allow research staff from the Trials Office at the University of Birmingham to look at the study records, including their medical records. It may be necessary to allow authorised personnel from government regulatory agencies (e.g. Medicines and Healthcare products Regulatory Agency (MHRA), the Sponsor and/or NHS bodies to have access to patient medical and research records. This is to ensure that the study is being conducted to the highest possible standards. Anonymised data from the study may also be provided to other third parties (e.g. the manufacturer of the trial treatment) for research, safety monitoring or licensing purposes.

The Investigator must maintain documents not for submission to the Trials Office (e.g. Patient Identification Logs) in strict confidence. In the case of specific issues and/or queries from the regulatory authorities, it will be necessary to have access to the complete trial records, provided that patient confidentiality is protected.

